## Procedures

Given the need for a comprehensive understanding of the local community to plan a specialist outreach clinic effectively, this study will be conducted in phases to assess prevalence, healthcare needs, and resource availability. This is crucial for establishing a specialized outreach clinic in a village. [16].

The initial phase of the research will entail the gathering of fundamental data from the twelve villages adopted by SRMIST namely, Kolathur, Chettipuniyam, Orathur, Nattarsanpattu, Anjur, Thenmelpakkam, Pattaravakkam, Kalivanthapattu, Baburayanpettai, Minnal Chithamur, Kilathivakkam and Chunambedu.

The fundamental details will include information on the number of panchayats (basic governing institution in Indian Villages), anganwadis(Rural child care centre in India), and the demographics of preschool children registered in Anganwadi.

Subsequent to the fundamental data collection and establishment of a rapport with the Panchayat authorities and Anganwadi personnel, a preliminary screening will be conducted by physiotherapists on all Anganwadi children aged between 3 to 5 years in 12 SRM UBA adopted villages after obtaining the parental consent. This screening aims to comprehensively enumerate data for determining the prevalence of Neurodevelopmental Disorders (NDD) among these children. The rapport established with village authorities will help in gaining confidence of common people and will help in improving their adherence.

Physiotherapists, in collaboration with parents, will complete a screening checklist. This checklist will primarily focus on detecting developmental delays, DCD, autism, and ADHD, as these are the most commonly observed NDDs among preschoolers. Information on children previously diagnosed with NDD and their history of treatment/rehabilitation will be gathered retrospectively.

Upon identifying the prevalence of neurodevelopmental disabilities, model centers will be established in villages with high prevalence rates. Consideration will be given to ensuring that these centers are accessible to the entire population, including nearby villages by discussing with the village heads. The establishment of model clinics will be based on the identified needs. While the initial plan is to set up one model center, if the prevalence is high and there is a demand, multiple model centers will be established by clustering the villages based on NDD distribution.

The model center, or specialist outreach center, is envisioned to have trained physiotherapists for children's rehabilitation, with pediatric physicians visiting the centers for progress checks and further evaluations. Equipped with essential tools such as swiss ball, peanut ball, obstacle for gait training, balance boards,etc., the center will provide pediatric rehabilitation and group therapies for children. Discussions and arrangements will be initiated with village authorities to position the model center close to or within school/Anganwadi premises.

Subsequent to NDD identification in children, baseline assessments of NDD will be conducted alongside qualitative assessment of caregivers' perspectives and experiences regarding accessing rehabilitation services in the community. Quantitatively, caregiver burden will be evaluated using a caregiver burden scale.

Upon enrollment, children will undergo physiotherapy rehabilitation for one year under a trained physiotherapist, with routine screenings by pediatricians. The neurodevelopmental rehabilitation will include sensorimotor training, motor learning, sensory integration, motor training and neurodevelopmental therapy which will be tailored according to the individual’s needs and the severity and type of disorder. Treatment will be given in person, in group or as individual therapy. The entire timeline and flow have been illustrated in Table 1.

**Table 1 Tab1:** Spirit timeline for the study

	Enrolment and allocation		Post allocation				Endline evaluation	Close-out
Time point	− t1	t0	t1	t2	t3	t4	t5	t7
Preliminary screenings	X							
Parental consent	X							
Analysis of prevalence	X							
Eligibility screen		X						
Obtained signed parental consent		X						
Allocation		X						
Baseline assessments		X						
Establish model centre		X						
One year rehabilitation			X	X	X	X		
Routine follow up screenings by pediatricians			X	X	X	X		
Baseline tools	X	X					X	
Effectiveness of intervention		X					X	
Caregiver burden		X					X	
Data entry and analysis	X						X	
Share findings with authorities	X							X
Final reports								X
Plan future studies								x

Each t indicates 3 months of time span

Treatment dose, intensity and sessions will be modified based on functional goals. After the year-long intervention, children and caregivers will undergo an end-line evaluation to gauge the effectiveness of the specialist outreach/model clinic in improving children with NDD and alleviating caregiver burden which will be assessed by the Physiotherapist who provided rehabilitation.

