Previous research has focused on estimating the prevalence of disabilities among preschool children in Western regions, leaving a significant data gap on the challenges faced by caregivers and disabled preterm children in Tamil Nadu. This lack of evidence hampers the development of policies, model outreach clinics, and support systems for parents and guardians of preterm children with disabilities, potentially leading to preventable long-term complications due to delayed access to healthcare and screening.

Given the increasing rate of NDD in early childhood and lack of accessibility it is imperative to regularly screen children for potential risk factors and provide timely interventions to prevent long-term complications particularly in rural areas with limited access to specialist care.

A two-step approach involving screening and definitive testing at healthcare facilities, along with standardized assessments for early identification of developmental abnormalities, is crucial for improving outcomes in children with NDD.

SRM Institute of Science and Technology (SRMIST) Kattankulathur, in alignment with the developmental goals of Unnat Bharat Abhiyan (UBA) has launched UBA-SRMIST in 2019 under the guidance of the University Grants Commission/ Ministry of Human Resource and Development/ All India Council for Technical education. UBA-SRMIST has adopted twelve rural villages in Kancheepuram and Chengalpattu and has conducted several welfare programs including awareness camps, screening programs and providing COVID-19 vaccination.

This study aims to evaluate the developmental outcomes of preschool children in twelve adopted villages of UBA-SRMIST, Kattankulathur, and provide early intervention programs by establishing a specialist outreach/model clinic which will help to uplift the village and generate data that can inform policies and interventions aimed at supporting parents, enhancing accessibility, and reducing the  burden of caregiver.

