## Primary objectives

To assess the prevalence of neurodevelopment disorder among children in the UBA adopted villages of SRMIST.

To develop a model physiotherapy centre and assess its impact on reducing the burden among the caregivers of children with neurodevelopmental disorders in rural areas of Tamil Nadu.

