## Materials and methods

### Participants

A single arm study will be conducted among children aged 3 to 5 years attending Anganwadi centers in SRM UBA adopted villages who will be screened for neurodevelopmental disorders with parental consent. Those identified with NDD or previously diagnosed with any form of NDD will be included in the study.

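### The first primary objective is called NDD prevalence, but the figure produced at −t1 is a proportion of unconfirmed screen-positives and probably overstates it

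*Protocol article*

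**What the plan says.** - **Objective.** Primary objectives lists first: "To assess the prevalence of neurodevelopment disorder among children in the UBA adopted villages of SRMIST".
- **Source of the figure.** Procedures: "Physiotherapists, in collaboration with parents, will complete a screening checklist". "This checklist will primarily focus on detecting developmental delays, DCD, autism, and ADHD". On its purpose: "This screening aims to comprehensively enumerate data for determining the prevalence of Neurodevelopmental Disorders (NDD) among these children".
- **Tools.** The Little DCDQ, ASQ-3, ADHD Rating Scale IV (preschool) and ISAA are the measures given for preliminary screening. No rule for combining them is stated.
- **Timing.** Table 1 marks preliminary screening, analysis of prevalence and a first sharing of findings with authorities at −t1. The eligibility screen, baseline assessments and establishment of the centre are at t0.
- **Use.** Procedures: "model centers will be established in villages with high prevalence rates". More than one centre may be opened if prevalence is high and there is demand.
- **Enrolment.** Participants: "Those identified with NDD or previously diagnosed with any form of NDD will be included in the study".
- **Confirmation.** The Background names "A two-step approach involving screening and definitive testing at healthcare facilities", along with standardised assessments, as crucial. In Procedures, paediatricians appear in connection with the centres, "with pediatric physicians visiting the centers for progress checks and further evaluations", and in Table 1 at follow-up from t1 to t4.

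**The concern.** The rationale describes two steps, but the primary estimate uses only the first. Procedures and Table 1 fix both the source and the timing of the prevalence figure, and both come before any step at which a newly identified child's diagnosis could be confirmed. This is what the article states, not a detail it leaves to a fuller document.

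A screen's positive rate equals prevalence only if its false positives and false negatives happen to balance. When most screened children are unaffected, even a modest false-positive rate outweighs the missed cases. Followed as written, the study would report a screen-positive proportion under the name of NDD prevalence, give it to authorities, and use it to decide where centres go and whether more than one is needed.

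**Working it through.** The article states no expected precision, sensitivity or specificity for the screen, so there is no figure of the plan's own to reproduce. The check asks how far a screen-positive proportion can lie from true prevalence.

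**Inputs**
- True prevalence p = 12.5%: the Abstract's 1 in 8 children under 6.
- True prevalence p = 2%: the Background's figure for Tamil Nadu. It refers to any form of disability, not NDD, so it serves only as a low scenario.
- Sensitivity (Se) and specificity (Sp): **assumed**, set equal, 0.80 to 0.95. The article says only that ASQ-3 is high on both.
- The four tools are treated as one composite screen.

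**Formulas**
- Apparent prevalence AP = p × Se + (1 − p) × (1 − Sp)
- Share of screen-positives who are true cases, PPV = p × Se / AP

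| True p | Se = Sp | AP | PPV | AP / p |
|---|---|---|---|---|
| 12.5% | 0.80 | 0.1000 + 0.1750 = 27.5% | 36% | 2.2 |
| 12.5% | 0.90 | 0.1125 + 0.0875 = 20.0% | 56% | 1.6 |
| 12.5% | 0.95 | 0.1188 + 0.0438 = 16.3% | 73% | 1.3 |
| 2% | 0.80 | 0.0160 + 0.1960 = 21.2% | 7.5% | 10.6 |
| 2% | 0.90 | 0.0180 + 0.0980 = 11.6% | 16% | 5.8 |
| 2% | 0.95 | 0.0190 + 0.0490 = 6.8% | 28% | 3.4 |

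**When would the screen not overstate?** AP ≤ p requires Sp ≥ 1 − p(1 − Se)/(1 − p). With Se assumed 0.85:
- p = 12.5%: 1 − 0.125 × 0.15/0.875 = 0.979
- p = 2%: 1 − 0.02 × 0.15/0.98 = 0.997

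**What a correction does.** The Rogan-Gladen estimate is (AP + Sp − 1)/(Se + Sp − 1). For an observed 20.0%:
- Se = Sp = 0.95: 0.15/0.90 = 16.7%
- Se = Sp = 0.90: 0.10/0.80 = 12.5%
- Se = Sp = 0.85: 0.05/0.70 = 7.1%
- Se = Sp = 0.80: 0/0.60 = 0%

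The same observed figure is thus compatible with a wide range of true values.

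**What confirming positives does.** With a perfect definitive test applied to screen-positives only, the count becomes p × Se. At Se = 0.90 that is 11.25% for a true 12.5%, and 1.8% for a true 2%. False positives are removed, but missed cases are not recovered.

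**The case against.** Several points against the concern have force.

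- **The two-step sentence is background.** It ties the approach to better outcomes for children and does not lay down a rule for estimating prevalence. That weakens the charge of contradiction. It does not change what the −t1 figure measures.
- **Enrolment may include confirmation.** A reader might infer that unconfirmed children are certainly enrolled. The documents do not show this: Table 1 has an eligibility screen at t0 whose content is not described, the Abstract speaks of children diagnosed with NDD, and previously diagnosed children enter with a diagnosis. The −t1 estimate still precedes that step.
- **Siting.** A reader might infer that villages would be wrongly ranked. Since AP = p(Se + Sp − 1) + (1 − Sp), AP rises with p whenever Se + Sp exceeds 1, so the expected ranking holds if Se and Sp are similar across villages. Differences between villages shrink (by a factor of 0.70 at 0.85/0.85), and the level that bears on opening further centres is affected, but a wrong order is not shown.
- **Caregiver burden.** A reader might infer that unaffected children would look improved at t5. Families are not selected on burden, and caregivers of unaffected children may start low and dilute any change. The direction is unknown.
- **Any one of four tools.** Counting a child positive on any tool would give larger figures: with four independent tools at Sp 0.95 (0.95⁴ = 0.815) and Se 0.90, AP is 27.5% at a true 12.5%. No such rule is stated, so the point does not rest on it.
- **ISAA is described as diagnostic.** That is so, but it covers one of the four conditions and is listed for preliminary screening.
- **Overstatement is not certain.** Specificity above the thresholds shown would reverse it, and the checklist's main focus on four conditions leaves out others named in the Background, such as visual impairment. Hence probably, not necessarily.

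**Conclusion.** The concern holds for the prevalence estimate. As written, the first primary objective is answered by a proportion of unconfirmed screen-positives, an unknown share of them false, analysed and first shared before any confirmation is described. Upward bias is the likely direction. With Se and Sp assumed equal at 0.80 to 0.95, the apparent figure is 1.3 to 2.2 times a true 12.5% and 3.4 to 10.6 times a true 2%. These sizes illustrate the problem and depend on the assumed accuracy and on treating the tools as one screen. That the figure is mislabelled does not depend on them.

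The verdict does not extend to enrolment without confirmation, to a wrong ranking of villages, or to spurious improvement in caregiver burden.

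**What to change.** 1. **Relabel.** Report the −t1 result, in the analysis, in the conclusions and in what goes to authorities, as the screen-positive proportion. Give it by tool and separately from previously diagnosed children. If a composite is also reported, state how the tools are combined.
2. **Correct.** Give a Rogan-Gladen corrected prevalence over a stated range of sensitivity and specificity, with the source of that range.
3. **Reserve the term.** Use NDD prevalence only for confirmed or previously diagnosed cases. Where feasible, have the paediatricians already in the plan confirm screen-positives before that estimate is reported. Confirmation only at t0 would come after the −t1 analysis, so Table 1 would need a later entry for confirmed prevalence.
4. **State the limit.** Confirming positives alone still misses false negatives.

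**Cost.** Items 1, 2 and 4 change reporting only and are nearly free. Item 3 may need extra paediatric time: under the assumptions above, 7% to 28% of screened children would be screen-positive. The headline prevalence will be smaller and less certain.

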## Outcome measures

### Primary outcome measures

#### Caregiver Burden Scale

The Caregiver Burden Scale is a measurement tool developed by Vadivelan K et al., through empirical analysis involving caregivers of children with disabilities in Tamil Nadu, considering sociocultural factors. It comprises 15 items rated on a 5-point Likert scale, ranging from 'strongly disagree' (1) to ' strongly agree' (5) [5]. This scale has demonstrated strong internal consistency, with a Cronbach's alpha exceeding 0.8. [17]. The higher the burden, lesser the quality of life.

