## Discussion

The anticipated primary outcome of the research will focus on the influence of the model center on reducing the burden among caregivers of children with NDD in the adopted villages affiliated with SRM Institute of Science and Technology, situated in Kattankulathur. Moreover, alongside the dissemination of the research findings, it will facilitate the strategic development of specialized services and the provision of care, as well as the appropriate referral of patients to higher levels of healthcare as necessary.

The Indian government has initiated UBA Scheme for the upliftment of rural villages. The primary objective of the UBA scheme is to engage higher educational institutions in research and understanding the realities of these communities at grass root level to contribute to the development of the village.

SRMIST under UBA has signed a Memorandum of Understanding with the Tamil Nadu State Institute of Rural Development and Panchayat Raj (SIRD&PR). The aim of the MoU was aligned with nine Local Sustainable Developmental Goals (LSDG) which included healthy village and child friendly village.

This research tries to fulfil these objectives by involving health care professionals in village level care via which both hospitals will be benefited by understanding the realities and also the village will be uplifted by reducing disability and caregiver burden. Also, the establishment of local outreach centre will help reducing the time and travel burden of parents making sure that the child receives treatment to the maximum.

The findings of this investigation will yield essential data concerning the frequency of developmental irregularities and disabilities among preschool children in twelve adopted villages linked with SRM, located in Kattankulathur. This data has the potential to steer the formulation of suitable strategies and protocols for the early implementation of rehabilitative measures, thereby alleviating the burden of disability among preschool children.

Furthermore, this study can act as a blueprint for establishing similar centers in various regions within Tamil Nadu. The data gathered will serve as a compass for governmental bodies and healthcare agencies in devising pertinent strategies and protocols to mitigate the prevalence of disability among children in Tamil Nadu.

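### The treating physiotherapist assesses the caregiver-reported primary outcome at end-line, so the single-arm pre-post change can include a courtesy effect that the analysis cannot separate from benefit

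*Protocol article*

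**What the plan says.** - **Who assesses.** The Procedures section describes the final assessment thus: "After the year-long intervention, children and caregivers will undergo an end-line evaluation to gauge the effectiveness of the specialist outreach/model clinic". The same sentence ends by naming the assessor: "alleviating caregiver burden which will be assessed by the Physiotherapist who provided rehabilitation". The relative clause may refer to the whole evaluation or to caregiver burden alone. On either reading the primary outcome is covered.
- **What is assessed.** The Caregiver Burden Scale is the only instrument under the primary outcome heading: "It comprises 15 items rated on a 5-point Likert scale", with answers running from strong disagreement to strong agreement. The Discussion confirms its standing: "The anticipated primary outcome of the research will focus on the influence of the model center on reducing the burden among caregivers".
- **Design.** Under Participants: "A single arm study will be conducted among children aged 3 to 5 years". The Statistical analysis section applies a t-test to burden scores before and after the intervention, and a logistic regression to a yes/no reduction in burden.
- **Timing.** Table 1 places caregiver burden at t0 and t5, with rehabilitation from t1 to t4. Between the two measurements, "children will undergo physiotherapy rehabilitation for one year under a trained physiotherapist".
- **Baseline assessor.** The article does not say who collects the burden scale at t0, nor whether it is self-completed or read out at either time.

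**The concern.** Burden is what the caregiver chooses to report. At t0 there is no year of treatment behind the conversation. At t5 the scale is in the hands of the person who treated the child for that year, and its stated purpose is to find out whether the clinic worked. A caregiver may soften answers out of courtesy to that therapist. If the therapist also reads out or records the items, the therapist's expectations can add to this.

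A concurrent control arm handled in the same way could cancel such a shift. This study has none, so the shift goes straight into the pre-post difference. The yes/no reduction outcome is built on the same scores and carries it too. Table 1 also repeats the baseline tools at t5. The Little DCDQ and ASQ-3 are described as parent-completed, and the ADHD scale has a parent-rated version, so the child results may be exposed in the same way.

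What is at stake is the main claim. The article expects the study to show that the model centre is effective, and offers it as a pattern for other regions and a guide for government.

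**Working it through.** The article gives no sample size, SD, effect size or error rate for this comparison, so there is no figure to reproduce. The check has a textual part and an illustration.

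**1. Is the choice fixed in the text?** Yes. The assessor is named outright for end-line, so this is not a detail left to a fuller document. No independent assessor is named anywhere. Paediatricians visit for progress checks and screening but are not given the outcome assessment.

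**2. What differs between t0 and t5?**

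| | t0 | t5 |
|---|---|---|
| Assessor of burden | not named | treating physiotherapist |
| Year-long treating relationship | absent | present |
| Mode of completion | not stated | not stated |
| Concurrent control | none | none |

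The second row holds even if the same physiotherapist collects the scale both times. The observed mean change is the true change plus any shift caused by that relationship. With one arm and two time points the two parts cannot be estimated separately.

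**3. Illustration on the scale (all inputs assumed except the 15 items and the 1-5 scoring).** If the items are summed, the range is 15 × 1 = 15 to 15 × 5 = 75.
- Assumed shift of 0.1 to 0.3 points per item: 15 × 0.1 = 1.5 points to 15 × 0.3 = 4.5 points.
- Assumed SD of 8 to 12 points: smallest ratio 1.5/12 = 0.13 SD; largest 4.5/8 = 0.56 SD. The upper end pairs the largest shift with the smallest SD.

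**4. Illustration of false-positive risk.** Assume no true change, a paired analysis at two-sided 5%, and a shift of b in SDs of the change score. This is a different SD from the one in step 3. The chance of a significant reduction is approximately

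P = Φ(b√n − 1.96).

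For b = 0.2 and n = 50: 0.2 × 7.071 − 1.960 = −0.546, and Φ(−0.546) = 0.293.

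| b | n = 30 | n = 50 | n = 100 | n = 200 |
|---|---|---|---|---|
| 0 | 2.5% | 2.5% | 2.5% | 2.5% |
| 0.1 | 7.9% | 10.5% | 16.9% | 29.3% |
| 0.2 | 19.4% | 29.3% | 51.6% | 80.7% |
| 0.3 | 37.6% | 56.4% | 85.1% | 98.9% |

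The exact noncentral t gives values up to about 2 percentage points lower for b = 0.1 to 0.3 (for example 28.3% at b = 0.2, n = 50). The values of b and n are chosen, not taken from the article. What does not depend on them is the pattern: a fixed shift does not shrink as n grows, so a larger study is more likely to call it significant.

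**The case against.** Much of the case on the other side stands, and it limits the point.

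- **Direction.** A reader might infer that the bias always favours the clinic. The article does not support that. Caregivers may hold back with an unfamiliar assessor at t0 and disclose more to a trusted therapist a year later; the Discussion itself mentions stigma. They may also stress continuing need so that the centre stays open. Lower reported burden is the most plausible direction, not a certain one.
- **Confounding with time.** A reader might infer that the rater changes between t0 and t5 and is perfectly confounded with time. The baseline assessor is not named, and physiotherapists already work with parents at screening ("a preliminary screening will be conducted by physiotherapists on all Anganwadi children aged between 3 to 5 years"), so it could be the same person. Only the treating relationship is known to change.
- **Gratitude for a free service.** The article does not say that the service is free, so this cannot be part of the argument.
- **Observer bias on the burden scale.** The items are the caregiver's own answers and the mode is not stated. If the scale is self-completed, therapist scoring adds little. Courtesy bias is then the mechanism that remains, provided the therapist still collects the form.
- **Size.** Every magnitude above follows from chosen inputs.
- **What a fix achieves.** Caregivers would still know that the child was treated, and maturation and regression to the mean would remain. Much of the difficulty in interpreting a positive result comes from having no control arm.

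None of this answers the core point. The protocol names the treating therapist as end-line assessor of a subjective primary outcome, and this source of bias can be avoided without changing the design.

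**Conclusion.** The concern holds in a limited form. As written, the plan exposes the primary pre-post change to a shift from the treating relationship, most plausibly towards lower reported burden, and the analysis cannot separate it from a true effect. This rests on three stated facts: the named end-line assessor, a caregiver-reported scale and a single-arm comparison over time.

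The size is unknown. The 0.13 to 0.56 SD range and the false-positive rates show what would follow from assumed shifts; they do not estimate what will happen here. It would also go too far to conclude that a positive result would be due to the assessor, or that changing the assessor would make the result interpretable as a causal effect. The article supports neither. The change should be made, preferably before baseline burden data are collected so that both time points match, but it addresses one avoidable bias among several limits of the design.

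**What to change.** Replace the end-line assessor rule in Procedures as follows.

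- **Primary outcome.** The caregiver completes the burden scale privately at both t0 and t5 and returns it sealed, not through the treating physiotherapist.
- **Where reading aloud is needed.** A physiotherapist already in the study who does not treat that child reads the items, in the same mode at both times. An Anganwadi worker is a less suitable reader: the centre may sit on or near Anganwadi premises, and the study builds rapport with those staff, so neutrality is unclear.
- **Child tools.** A non-treating study physiotherapist administers or scores them, again in the same mode at t0 and t5. For the parent-reported tools this takes the treating therapist out of the exchange, but the parent still knows about the treatment.
- **If only one physiotherapist is available** (the initial plan is one centre), keep sealed self-completion for the primary outcome and state the limitation for the child tools.

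The article refers to physiotherapists in the plural for both screening and the centre, so where more than one is available this is a swap of tasks that leaves treatment untouched. The cost is some scheduling at t0 and t5 and the handling of sealed forms. The report should still name maturation, regression to the mean and the caregiver's knowledge of treatment as remaining limits.
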